### Modeling

To target individuals’ self-efficacy to carry out the desired behavior change and the corresponding plans (PO 6, 7, 8, and 10), modeling techniques are used. Narratives are used as a practical application for modeling. A narrative is a constructive format in which a sequence of events is described [59]. For each sub-behavior, two narratives are created. The narratives follow a chronological storyline in which a role model tells how his/her behavior change is going and how he/she deals with encountered difficulties. Each story consists of implicit tips and participants can choose whether they want to view these stories. In line with the parameters of modeling, all narratives show people who are struggling with their behavior change but eventually succeed in achieving their goal [40]. In the text-text intervention, the narratives merely consist of text, while the narratives in the video-text intervention are displayed by means of videos. In these videos an actor plays the role of a model (i.e. a person who also used the program). A different actor is used for each of the eighteen narratives in order to increase the credibility of the stories. To ensure that participants can identify themselves with the persons in the narratives, we used a variety of actors with differences in ethnic background, age, gender, educational level, and BMI. In the text-text intervention, these characteristics were described in text in the introduction of the narratives.

### Reinforcement and external attribution

Besides modeling, participants’ self-efficacy will also be targeted by means of reinforcement and external attribution. During the interventions, the progress toward enactment of plans and goal achievement of the participants will be evaluated. This evaluation will, for example, assess whether participants have gained, maintained, or lost weight (PO 7) as well as whether or not they have improved their physical activity level and/or dietary intake (PO 8). Participants who achieve their goals successfully will be complimented, while those who fail to achieve their goals will receive feedback in which the failure will be attributed to external factors that people cannot control in order to prevent a decrease in self-efficacy [60]. In the video-text intervention, this feedback will be provided by means of a video message, in which the progress of an individual is discussed. Simultaneously with the video message, a table is shown below the video consisting of an overview of participants’ changes in body weight and dietary intake and/or physical activity during the program. In the text-text intervention, the same table will be provided, but then accompanied with text-based messages.

### Step 4: program development

### Scope and sequence

The program consists of six sessions. Six sessions was considered to be sufficient to go through all phases of the I-Change Model and self-regulation theories. Figure 1 provides a flowchart of the six sessions, including a brief description of their content. In session one, participants have to decide whether they want to maintain their current weight or lose a little weight and how they want to achieve this goal: improving their physical activity level, dietary intake or both (PO 1 and 2). In session two, participants have to decide which specific sub-behaviors they want to change and how (PO 2), followed by the formation of action and preparatory plans (PO 3). It should be noted that the content of session one and two could have been combined into one large session, but because too much feedback may become too extensive for people to process [23], it was decided to use two separate sessions. However, at the end of session one, participants can decide to continue with session two directly. After session two, participants can start with enacting their plans and performing the desired behavior (PO 4 and 5). The remaining four sessions can be accessed in the next weeks, with at least one week between the sessions. The date for visiting the next sessions can be chosen by the participant. The focus of these sessions is on evaluating the progress toward meeting the weight and behavior change goals and enactment of the action plans and helping participants to deal with encountered or expected difficulties, for which they can make coping plans (PO 6, 7, and 8). In session four and five, participants have the possibility to change their goals and/or action plans (PO 9) and correspondingly go back to session two. In session four, five, and six, participants can further choose whether they want to view the narratives, which can help them in generating ideas for coping plans. Finally, the sixth session gives additional attention to how to maintain the behavior change on the long-term (PO 10). In total, participants can use the assigned intervention for a period of maximum three months, which is sufficient to follow all sessions. Each session lasts approximately 15 minutes, even though session two (in which current behavior is assessed) may take a bit longer to complete.

**Figure 1 F1:**
[figure not shown]
Overview of the content of the intervention.

### Development

The two interventions are developed using the Tailorbuilder software (OSE, the Netherlands), a program which is specifically designed to develop web-based computer-tailored interventions. To enhance participant retention and outcomes [61], the interventions are integrated into a website (http://www.gewicht-in-balans.info). This website provides information about the study, the intervention, and answers to frequently asked questions. Participants have to log in to the website in order to use their assigned intervention. Once logged in, participants also have the opportunity to read information and advices from previous sessions.

For the video-text intervention 240 videos were recorded. Because of budgetary constraints it was unfortunately not possible to convert all educational messages into videos. In all video messages an actor reads the messages aloud (i.e. the text in the text-text intervention). The video messages related to physical activity were recorded in a gym and given by a professional male actor, while the messages related to dietary intake were recorded in a cooking studio using a professional female actor. These two actors had the role as an expert in the field of nutrition and physical activity. For the narratives, two actors per sub-behavior were recruited, who each had to act in three videos. These videos were recorded in a film studio that was decorated as a living room in order to increase the authenticity of the stories.

An example of the text-text intervention and the video-text intervention can be found in Additional file 2 and Additional file 3.

### Pretest of the interventions

Two pretests were conducted before a definite version of the interventions was developed. First, a prototype of the text-text intervention was pretested among 25 members of the target population. Twenty individuals worked through the intervention at home, while five participants participated in a cognitive interview in the presence of a member of the project team. During this interview, participants were asked to talk out loud about the choices they made in the program and about their interpretation of the feedback, usability of the action planning tools and so on. This process yielded useful findings, for example about log in problems and unclear questions and feedback. Based on these findings, the text-text intervention was improved after which the videos were recorded. Subsequently, a pretest of the video-text intervention was conducted using the same procedure as the first pretest. This second pretest, however, focused more on the clarity of the video messages as well as the usability of the website in which the interventions are integrated. This pretest again resulted in several useful suggestions for improvement, such as speed problems during the program and difficulties with navigation through the website.

### Step 5: planning for program implementation

The purpose of step five is to develop a plan for program use, including adoption, implementation, and continuation. The need to facilitate program use was, however, already taken into account from the beginning of step one by developing the interventions in such a way that will enhance their potential for being adopted, implemented, and sustained. For example, to implement the interventions no human actions are required. Individuals who want to use the intervention can go the website and register, after which they will automatically receive programmed e-mails. Furthermore, the development process of the interventions may also increase the likelihood of program use. For example, several small pilot studies among members of the target population were conducted to identify the preferences and needs of the potential users regarding the content of the intervention, the visual aspects of the website and intervention, the format of making preparatory, action, and coping plans, the recruitment materials for the evaluation study (e.g. brochure), the included difficult situations, the name of the intervention, and the actors in the video messages. During these pilot studies, we particularly investigated the opinions of individuals with a low level of education to ensure their preferences are integrated in the intervention and all intervention parts were clear to them. Moreover, by pretesting the text-text intervention and subsequently the video-text intervention, we also tried to adapt the intervention as much as possible to users’ preferences and needs.

To further facilitate program use, we also composed an advisory board consisting of potential adopters and implementers, including several occupational health services. Occupational health services have the objective to provide both cure and care for working people, which is in line with the purpose of the intervention. In the Netherlands, many employees receive an annual medical screening carried out by an occupational health service [62]. During these medical screenings, employees can be handed over a brochure about the intervention. Other implementation possibilities could be the use of advertisements in mass media, social media, and newsletters in companies.

### Step 6: planning for program evaluation

### Evaluation design and procedure

A three-group randomized controlled trial will be conducted to evaluate the efficacy of both versions of the intervention in comparison to a waiting list control group on BMI, dietary intake, and physical activity. Participants who will be randomized to the control group can use one of the interventions after the study. Measurements will take place at baseline (T0) and at 6 (T2) and 12 months (T3) after baseline. During all measurements, participants will have to complete an online questionnaire via the study website.

A power calculation was carried out to estimate the required number of participants. In order to detect a medium sized effect (d = 0.5) on BMI [63], using a power of .90, a significance level of .05, and being able to test interaction effects between participants with a low, medium, and high level of education, about 1,000 participants need to complete the study. Taking into account a drop-out percentage of 50% between baseline and the last follow-up measurement [64], this implies that approximately 2,000 participants are needed at baseline. These will be divided over the three study arms equally. Participants are eligible for inclusion when they are at least 18 years old, have a job, and have a BMI between 18.5 and 30. Although obese people (BMI ≥ 30) do not belong to the target population for the evaluation study, these individuals will be given the possibility to use the program. Participants who have a physical condition that may influence dietary or physical activity patterns (e.g. diabetes) are ineligible to participate. Participants will be recruited by various occupational health services during medical screenings as well as through companies without interference of the occupational health services. Brochures and messages in internal company newsletters will be used to invite people to participate in the study. Mass media advertisements and press releases will also be used to recruit participants. After registration at the study website, participants will be randomized to one of the three conditions and have the opportunity to fill out the baseline questionnaire. Participants in one of the intervention conditions have to wait two weeks before they can start using their assigned intervention. To decrease the likelihood of attrition in the evaluation study, one hundred cash prizes of €100 will be raffled among participants who complete all questionnaires [54]. Participants will also receive two reminders per intervention session and per measurement in order to improve retention in the study.

The Ethical Commission of the Open University Heerlen reviewed the study protocol and judged that the study is not within the scope of the Social Support Act (WMO) and that no approval of the medical ethics committee was required. They also indicated that there was no objection to performance of the study. The study is registered in the Dutch Trial Registry (nr. NTR3501). Participants’ approval will be obtained in line with the APA informed consent ethical principles. At the beginning of the study, all eligible participants will be provided with information about the study and asked to sign an online informed consent form.

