### Measurement instruments

The primary outcomes of the study are self-reported body weight, BMI, physical activity, and dietary intake. These will be assessed at baseline and at 6 and 12 month follow-up. In a sample of the participants, body weight and height will also be measured objectively by various occupational health services at baseline and 12 month follow-up.

Further, several potential mediators and moderators of the intervention effects will be measured. Mediators (i.e. working mechanisms of the interventions) that will be assessed include self-regulation skills and self-efficacy and intention towards being more physically active and eating less of energy-dense food products. These will be measured at baseline and at 6 and 12 month follow-up. At baseline, various moderators will be measured as well, including demographic characteristics (e.g. gender, age, and educational level), information processing style, self-efficacy, intention, media preference, and perceived body image.

In addition, we will also conduct a process evaluation to examine potential moderating factors. This evaluation will take place directly after the last session of the intervention (T1) as well as briefly at the 6 month follow-up measurement (T2). Process measures that will be examined include action planning (i.e. the quality of action plans), intervention use (e.g. number of times participants logged in and amount of information viewed), and participants’ appreciation of the intervention (e.g. source, message, and channel factors). Figure 2 gives an overview of the concepts that will be measured at each time point.

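### With 50% loss expected at 12 months, doubling enrolment protects power but not against selective loss; a weight-only request to non-responders is a cheap addition

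*Protocol article*

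**What the plan says.** All of this is in Step 6 of the Protocol article.

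- **Outcomes** (Measurement instruments): "The primary outcomes of the study are self-reported body weight, BMI, physical activity, and dietary intake".
- **Timing** (Evaluation design and procedure): "Measurements will take place at baseline (T0) and at 6 (T2) and 12 months (T3) after baseline".
- **Route** (same section): "During all measurements, participants will have to complete an online questionnaire via the study website".
- **Sample size** (same section): the calculation is built on BMI, "In order to detect a medium sized effect (d = 0.5) on BMI", and concludes that "about 1,000 participants need to complete the study".
- **Loss** (same section): the allowance is worded as "Taking into account a drop-out percentage of 50% between baseline and the last follow-up measurement". For enrolment the article concludes from it that "this implies that approximately 2,000 participants are needed at baseline".
- **Retention** (same section): two reminders per measurement, and one hundred prizes of €100 raffled among participants who complete all questionnaires.
- **Measured weights**, taken at the first and last measurements (Measurement instruments): "In a sample of the participants, body weight and height will also be measured objectively by various occupational health services at baseline and 12 month". The size of this sample is not given, and no role is stated for these values when the 12-month online answer is missing.

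**The concern.** The expected loss is half of the randomised sample, and the sample-size answer to it is to recruit twice as many people. That restores the count of completers. It does nothing about which participants are lost.

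The article itself gives reasons why loss may not be neutral:

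- **Arm.** Controls are promised an intervention after the study, which is a reason to stay. Active participants may use theirs for at most three months, so access ends well before the 12-month measurement.
- **Programme drop-out.** The interventions sit in the study website, and the questionnaires are completed through that website. Someone who has given up on the programme must return to the same site to supply an endpoint.
- **Education.** The Background says that lower-educated people have lower literacy and that text works less well for them. The contrast between video and text by education is the first hypothesis.

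The raffle adds one more feature: a participant who misses the 6-month questionnaire no longer qualifies, so this incentive is gone at 12 months.

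At stake are the comparisons of each intervention with control, and the comparison of video with text within education levels. BMI, the outcome on which the trial is sized, is also the easiest to rescue. Height must already be held from baseline, because BMI is an entry criterion, so only a current weight is needed.

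**Working it through.** **1. The plan's own figure.** Completers needed 1,000; loss 50%.

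Baseline N = 1,000 / (1 − 0.5) = 2,000. This matches the article. I treat the 50% as the share without a 12-month online answer, so 1,000 non-responders are expected.

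**2. Power is not the problem.** Three equal arms give 1,000 / 3 ≈ 333 completers per arm. At 90% power and two-sided 0.05 (sidedness is not stated; two-sided is assumed), the detectable difference between two arms is

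(1.960 + 1.282) × √(2 / 333.3) = 0.251 SD,

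which is smaller than the planned 0.5 SD. The derivation of the 1,000 for the education interaction cannot be identified uniquely from the article, but this point does not depend on it.

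**3. Why doubling does not address bias.** Let L be the loss, taken as equal in the two arms compared. Let D_R and D_N be the true arm differences among responders and non-responders.

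- Effect in all randomised: (1 − L) × D_R + L × D_N
- Effect estimated from responders: D_R
- Bias: D_R − [(1 − L) × D_R + L × D_N] = L × (D_R − D_N)

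The number enrolled does not appear. At L = 0.5, half of any gap between D_R and D_N passes into the estimate, whether 1,000 or 2,000 are recruited. Loss that differs between arms would add a further term. The article gives no value for D_R − D_N, so the bias has no documented size.

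**4. What a weight-only request could add.** The recovery rate r is not in the document, so a range is assumed.

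- BMI available = 1,000 + 1,000 × r
- Remaining loss = 0.5 × (1 − r)
- Standard error reduction = 1 − √[1,000 / (1,000 + 1,000 × r)]

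| Assumed r | 12-month BMI available | Remaining loss | SE reduction |
|---|---|---|---|
| 10% | 1,100 | 45% | 4.7% |
| 20% | 1,200 | 40% | 8.7% |
| 30% | 1,300 | 35% | 12.3% |
| 40% | 1,400 | 30% | 15.5% |

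The detectable arm difference would move from 0.251 SD to 0.229 SD at 1,200 and 0.212 SD at 1,400.

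**5. What cannot be computed.** Bias would shrink in step with the remaining loss only if those recovered were a random draw from the non-responders. People who answer one more message may resemble responders more than they resemble those who stay silent. The reduction in bias therefore cannot be read from the table.

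**The case against.** The strongest reply is that this is a condensed article, mainly about intervention development, and that a last-step procedure for non-responders may be in the full protocol. The article contains no contradiction or arithmetic error here, and 50% is a cited planning assumption accompanied by two retention measures. Much of this stands, and it makes the point an improvement to the design, not the correction of an error. It does not remove the point, because the article itself states the collection route, the expected loss and the response to it, and that stated procedure can be improved cheaply.

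Several stronger readings are tempting but unsupported:

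- **That a non-responder has no 12-month BMI.** Members of the occupational-health sample may have weight and height measured at 12 months, and nothing makes this conditional on answering online.
- **That a long questionnaire must be finished in full.** Its length, item order and handling of partial answers are not given. Process measures are named after the last session and briefly at 6 months, not at 12 months.
- **That nothing happens after the second reminder.** The article is silent on this.
- **That the occupational-health weights could simply fill the gaps.** A measured follow-up set against a self-reported baseline would mix reporting mode with change, and only among non-responders. Recruitment also runs through companies without the occupational health services and through mass media, so the sample may reach few of those lost.

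**Conclusion.** The point holds as a cheap design improvement. The stated plan meets 50% expected loss by doubling enrolment, sending reminders and offering a raffle for complete responders. Doubling secures the 1,000 completers but leaves the estimate as exposed to selective loss as before, and no reduced-burden route to weight is stated.

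The quantifiable gain is modest and rests wholly on the assumed 10% to 40% recovery: 100 to 400 more participants with a 12-month BMI, and a standard error about 5% to 15% smaller. Because power is already provided for, the main reason to act is less exposure to bias on the outcome the trial is sized on. The document supports the direction of that concern through its own remarks on education, programme access and the waiting-list incentive. It does not show that selective loss will occur, nor how much bias a fallback would remove.

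**What to change.** **Evaluation design and procedure.** Add a last step at 6 and 12 months. After the second reminder, every non-responder in all three arms receives the same automated request for current weight and its date only, whether or not the assigned sessions were used. Flag these values by source and run a sensitivity analysis without them.

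**Measurement instruments.** State that the 12-month occupational-health measurement is sought for every member of the objective sample, whether or not the 12-month questionnaire is answered. Use it in a flagged sensitivity analysis of BMI change, and only against the same person's occupational-health baseline, so that self-reported and measured values are not mixed within a person.

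**Cost.** One automated message with a short form, plus a source flag. Programmed e-mails are already part of the system, and no extra staff, visits or participants are needed for the request. Diet and physical activity, which are also primary, remain missing for those recovered, and those who reply may not represent those who stay silent.
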